#### Epworth Sleepiness Scale (ESS)

A hard copy of ESS questionnaire was provided at each time point to assess the participant's general level of daytime sleepiness. The sum of scores from 7 daytime daily life situations gave the ESS score (range 0-24). The higher the score, the higher the chances of dozing during the day. Participants with a total score <5 were categorised as having a low likelihood of dozing, a score between 6-10 was categorized as having a higher likelihood of sleepiness during the day, between 11-12 and 13-15 was considered mild excessive and moderate excessive daytime sleepiness, respectively and a score  $\geq 16$  was categorised as severe excessive day time sleepiness.

**Outcome measure:** ESS total score

### Other secondary outcome measures

#### Gait

Kinetic data on gait were recorded when participants completed four trials of free walking (without breaks) on a pre-calibrated pressure sensitive 20 feet long (6.09 m) Zeno walkway (ZenoMetrics, LLC, Peekskill, New York). The data were collected at 120 Hz and analysed using ProtoKinetics Movement Analysis Software, version 5.08 (PKMAS; ProtoKinetics LLC, Havertown, PA). Data from the Zeno mat were processed, and artifacts removed using the PKMAS software.

**Outcome measures:** Stride velocity, Total double support

## **Balance**

To assess the postural balance, participants were asked to perform four randomly ordered tasks at each laboratory visit; (i) standing on a foam surface with eyes open and arms down; (ii) standing on a foam surface with eyes closed and arms down; Each task comprised four 30 s trials. Participants stood on a force plate during the tasks and the data was recorded using a Vicon Nexus (Vicon Motion Systems, Centennial, CO) system. The sampling rate of the force plate measurements was 1000 Hz. Participants were allowed to take breaks between trials. The vertical ground reaction force data from the force plate was converted into centre of pressure (COP) data using customized MATLAB codes. The average velocity of the centre of pressure (COPv) was defined as the sum of Euclidean distances between the differences in antero-posterior (AP) and medio-lateral (ML) forces divided by the total time.

*Outcome measures:* Average velocity of centre of pressure (CoP)

## **Tremor**

Data on tremor were recorded with two inertial measurement units (IMUs) attached to the index fingers of both hands while the participants completed two tasks; (i) sitting on a chair with resting arms, and; (ii) sitting on a chair with resting arms but index fingers pointing forwards. Each task had four 30 s trials. Participants were allowed to take breaks between the trials. Vicon IMeasureU BlueTrident sensors (IMeasureU, Auckland, New Zealand) were attached to the participants skin using double sided tapes. The IMUs recorded 3x three-dimensional (accelerometer, gyroscope and magnetometer) data at a sampling rate of 1125 Hz. The tremor data from the two IMUs were transferred to the computer and processed by the Vicon Nexus system and exported to the database. To process the accelerometer data, a 5-sample median filter was first applied to remove noise spikes from the x, y and z axes, then the main axis of tremor was identified using Principal Component Analysis. The first and last 2.5 s of data were removed to address any pre- and post-trial instability. A linear phase 4th order Butterworth band pass filter was applied at 0.5 Hz and 40 Hz and the power spectral density calculated by the Welch method. Acceleration values more than 6 standard deviations from the mean were removed and the missing values interpolated using a moving mean window. The location of dominant frequency for each trial was confirmed visually.

*Outcome measures:* Dominant frequency both hands for resting and postural tremor

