### Other Secondary (motor)

- Change from baseline to week 4 and week 6 in mean: stride velocity, total double support, balance (average velocity of centre of pressure) and dominant frequency both hands for resting and postural tremor

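### As described, PCA picks the tremor axis before trimming and band-pass filtering, so slow finger tilt can set the axis when tremor is mild and make the dominant frequency unreliable

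*Combined protocol and SAP*

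**What the plan says.** The motor endpoints under Other Secondary include "dominant frequency both hands for resting and postural tremor". The Tremor section of the Supplementary Methods names no other tremor outcome.

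That section describes the processing in this order:

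1. Spike removal, then axis choice: a 5-sample median filter served first to "remove noise spikes from the x, y and z axes, then the main axis of tremor was identified using Principal Component Analysis".
2. Trimming: "The first and last 2.5 s of data were removed to address any pre- and post-trial instability".
3. Filter and spectrum: "Butterworth band pass filter was applied at 0.5 Hz and 40 Hz and the power spectral density calculated by the Welch method".
4. Removal of acceleration values beyond 6 SD, with interpolation of the gaps.
5. Visual confirmation of the peak in each trial.

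Each task has four 30 s trials, sampled at 1125 Hz. Gyroscope and magnetometer data were recorded too, but no use of them to remove gravity is described. Protocol section 5.5 gives neither an axis rule nor a filter order for tremor; it refers to the group's established methods.

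**The concern.** PCA returns the direction of largest variance, whatever its frequency. An accelerometer on a finger senses gravity, so a slow change of finger angle adds variance far below tremor frequencies. The later high-pass edge at 0.5 Hz would take most of that out, but at the PCA step it is still present. If it exceeds the tremor variance, the first component points along the tilt, and tremor on that component is partly or wholly lost. The start and end of each trial, which are later discarded as unstable, also contribute to the axis choice.

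The outcome for both tasks and both hands depends on this step. Low-amplitude trials are plausible: the eligibility criteria do not require tremor, and protocol section 5.1 expects some participants who are not tremor dominant. Looking at the spectrum of a badly chosen axis cannot bring back tremor that lies off that axis, and no rule is given for trials without a clear peak.

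**Working it through.** The plan states no figure on this point, so there is none to reproduce. From the Tremor section: 1125 Hz, 5-sample median filter, 30 s trials, 2.5 s cut from each end, band-pass 0.5-40 Hz. Tremor amplitude, tilt, background noise and angles are assumptions.

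**What reaches PCA.** The median filter spans 5/1125 s = 4.4 ms, so slow drift passes. The untrimmed record includes 2 x 2.5 = 5 s of 30 s that is later discarded.

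**When tilt takes the axis.** Tilt of RMS angle θ adds about g sin θ of acceleration, with g = 9.81 m/s2. If tilt and tremor are orthogonal, the first component follows tilt whenever g sin θ exceeds the tremor RMS. For a 5 Hz tremor, peak displacement is √2 x RMS/(2π x 5)², and (2π x 5)² = 987.

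| Tilt RMS | g sin θ (m/s2) | Equivalent 5 Hz tremor, peak |
|---|---|---|
| 0.5° | 0.086 | 0.12 mm |
| 1° | 0.171 | 0.25 mm |
| 2° | 0.342 | 0.49 mm |
| 5° | 0.855 | 1.2 mm |

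**What a wrong axis does.** With angle α between tremor and the chosen axis, tremor power is multiplied by cos²α: 0.5 at 45°, 0.25 at 60°, 0 at 90°. The peak shrinks but does not move.

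**Simulation with linear tilt.** Tremor of 4-7 Hz on a random axis, a tilt ramp on another random axis, 1/f background of 0.03 m/s2 RMS per axis, 100 or 120 trials per cell. The entries are the share of trials with the Welch peak wrong by more than 0.5 Hz, given as the range over three runs with different settings.

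| Tremor RMS (m/s2) | 0.5° | 2° | 5° | Band-pass before PCA |
|---|---|---|---|---|
| 0.02 | 12-22% | 28-41% | 32-55% | 0% |
| 0.05 | 0% | 13-15% | 12-15% | 0% |
| 0.1 | 0% | 0% | 4-6% | 0% |
| 0.3 | 0% | 0% | 0% | 0% |

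A fourth run gave lower rates: 13-27% at 0.02, 8-10% at 0.05 with 2 to 5 degrees, 0-2% at 0.1 and 0% at 0.3. At 0.02-0.05 m/s2 with 2 to 5 degrees, the chosen axis kept 29-44% of tremor power, against 97-100% with the filter first.

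The pattern fits the closed form. Taking the tilt as the total change over the trial, a ramp has SD g sin θ/√12, which is 0.025, 0.099 and 0.247 m/s2 for 0.5, 2 and 5 degrees. Errors appear only where this exceeds the tremor RMS.

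**Simulation with random drift.** 60 trials per cell, random angle, tilt given as RMS, wrong by more than 1 Hz, median filter and 6 SD step left out. Drift with a 1/f⁴ spectrum stays almost wholly below 0.5 Hz; 1/f² drift spills above it. Entries are the described order / band-pass first.

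| Tremor RMS (m/s2) | 1/f⁴, 1° | 1/f⁴, 3° | 1/f², 1° | 1/f², 3° |
|---|---|---|---|---|
| 0.02 | 18% / 0% | 20% / 0% | 97% / 90% | 100% / 100% |
| 0.05 | 7% / 0% | 7% / 0% | 38% / 0% | 100% / 100% |
| 0.1 | 0% / 0% | 3% / 0% | 10% / 0% | 55% / 2% |
| 0.3 | 0% / 0% | 0% / 0% | 0% / 0% | 10% / 0% |

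Tilt set the axis in every trial at tremor up to 0.1 m/s2 with 1 degree and up to 0.3 m/s2 with 3 degrees. In those cells a tremor orthogonal to the tilt gave a wrong frequency in 100% of trials under the described order. At 45 or 60 degrees with 1/f⁴ drift it gave 0%, although the axis was wrong.

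**The case against.** A reader might infer that mild tremor generally yields a wrong dominant frequency. The documents do not support that. The band-pass comes before the spectrum, so most slow tilt is gone from the signal whose peak is read, and a tilted axis attenuates the peak without shifting it. The high error rates need very small tremor: 0.02 m/s2 RMS is below the assumed background of 0.03 m/s2 and equals about 0.03 mm peak at 5 Hz. They also vary with settings such as the Welch segment length, which the plan does not state. Tilt of 2 to 5 degrees is assumed as well; the Tremor section has participants seated with arms resting, although protocol section 5.5 describes postural tremor with the arms held out. A clean 0% after reordering depends on drift that stays below 0.5 Hz. All of this stands and limits the size of the point.

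A reader might also infer that values beyond 6 SD stayed in the spectrum because their removal is described last. That reads loose narrative as execution order: only the median filter and PCA are joined by words of sequence. The same looseness means that trimming or filtering might have been run earlier than written. Nor does the text say outright that the Welch spectrum was computed on the first component. These gaps call for confirmation of what was done. They do not make PCA on unfiltered acceleration sound.

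Finally, bias between arms might be inferred. The same processing serves both arms, so the expected effect is noise; bias would need tremor size or tilt to differ by arm or visit, and nothing in the documents shows that.

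**Conclusion.** The point holds in limited form. As written, the axis is chosen on acceleration that still contains slow tilt and the unstable trial ends, and a tilt of about 1 degree RMS is enough to capture it at tremor up to 0.1 m/s2 RMS. The dominant frequency then goes wrong mainly when tremor is nearly orthogonal to the tilt or when drift reaches above 0.5 Hz. With linear tilt of 0.5 to 5 degrees the error share is roughly 10-55% of trials at 0.02 m/s2, 0-15% at 0.05, 0-6% at 0.1 and 0% at 0.3. These figures rest wholly on assumed amplitudes, and on the described order being the executed one with the spectrum taken on the first component. Filtering first removes the errors when drift is slow, but does not rescue the weakest tremor when drift is fast. The effect is confined to the tremor part of the other-secondary motor outcomes. Primary outcomes and sample size are untouched.

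**What to change.** - Process each trial in this order: median filter, 6 SD step, trim, 0.5-40 Hz band-pass on x, y and z, PCA on the filtered axes, Welch on the first component. State the Welch segment length.
- Confirm the order that was run, including where the 6 SD step stood and which signal went into the spectrum. If trimming and filtering already preceded PCA, correcting the text is enough.
- If PCA did come first, re-derive the resting and postural outcomes, provided the three-axis recordings were kept (the documents do not say), and report how many trial values change. If they were not kept, report this as a limitation of the tremor results.
- Give a rule for trials with no clear peak, since reordering cannot recover the weakest tremor.

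The cost is one re-run of the tremor processing and a refit of the mixed models for these outcomes. No new data or visits are needed.

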### **2. Movement Disorder Society-Unified Parkinson's Disease Rating Scale (MDS-UPDRS)**

A hard copy of the UPDRS Patient Questionnaire (Part I- Non-motor Aspects and Part II- Motor Aspects of Experiences of Daily Living) was provided to the participant at each time point. Sections of the questionnaire on cognitive aspects (Part I), motor examination (Part III) and motor complications (Part IV) were administered by the same examiners at each time point. The sum of the scores from all four parts of the questionnaire gave the MDS-UPDRS Total score (range 0-260).

The Hoehn and Yahr score indicated the severity of Parkinson's disease (range 0-5) at baseline. The sum of the scores from Part III gave the UPDRS Motor score (range 0-132). The higher the scores, the worse the Parkinson's Disease-related disability and impairment.

**Outcome measure:** MDS-UPDRS Total score, MDS-UPDRS Motor score

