## 2. Study objectives

### 2.1. Research questions/ aims

The primary aim is to determine the effect of melanopsin-directed light therapy (daylight melanopsin and enhanced melanopsin) on circadian/sleep behaviour and motor (i.e. gait, balance, tremor) function in optimally medicated people with PD.

The secondary aim is to objectively quantify melanopsin function and its link to circadian and sleep behaviour in PD to define the underlying physiological mechanisms mediating the effect of light in PD.

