## 3. Study design

- This is a randomised controlled double-blind, clinical intervention study that investigates the effect of melanopsin-directed light on non-motor and motor function in people with Parkinson's disease.
- Study methodology  
Light, as the primary driver of circadian function, is transmitted by melanopsin cell photoreceptors in the eye to synchronize the circadian pacemaker (the body clock) in the brain (suprachiasmatic nucleus, SCN) to the day/night cycle. Our preliminary evidence reveals that people with PD with melanopsin dysfunction have aberrant light input to the SCN; this study will show that melanopsin cell dysfunction progresses with disease stage and leads to increased susceptibility to circadian disruption that consequently exacerbates non-motor and motor symptoms. By *objectively determining melanopsin photoreceptor function at different PD stages and simultaneously assessing circadian and sleep disruption*, we will demonstrate that people with PD who are exposed to melanopsin-directed lighting during daytime hours over a 4 week period will have (i) *improved circadian behaviour* and (ii) *improved sleep and motor function*.

This research will provide the missing, evidence-based data for understanding the impact of supplemental light exposure on PD. By defining the effect of melanopsin cell dysfunction in circadian and sleep disruption in people with PD, we will provide the foundation knowledge in this emerging research field and the guiding principles for the clinical application of supplemental bright light. In the longer term, the study outcomes will impact lighting industries to expand the translation of supplemental lighting technologies through integration of "PD lights" into homes. This research will directly impact on people with PD and empower self-control of the condition using a simple and original solution that adjusts melanopsin light exposure to improve the lives of those with PD.

- Research project setting  
Medical Retina and Visual Science Laboratories and the Movement Neuroscience Laboratories at Queensland University of Technology.

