 Gait: Participants will walk at their own pace for 2 trials on a firm surface with bare feet. Walking will be recorded using a ProtoKinetics pressure sensitive matt that records temporospatial parameters of gait (e.g. velocity, stride length, stride time variability and cadence). Upper body motion (i.e. medio-lateral) and arm swing will be recorded using inertial sensors. These parameters are established as important indicators of dynamic postural stability during locomotion in PD.  
 Balance & Tremor: These will be assessed utilizing methods previously established by our group. Standing balance will be assessed on a force plate (100Hz) on a firm and a foam surface with eyes open and closed (4 trials of 30s). Force plate centre of pressure in the medio-lateral and anterior-posterior direction provides an objective measure of postural stability. Tremor assessment will be undertaken with arms relaxed by participant’s side (for resting tremor) and while holding arms out in front (postural tremor); accelerometers are placed on the left and right fingers to record movement. Tremor will be quantified from the accelerometer signals in the time and frequency domain using our previously established methods. Tremor assessment contributes to objective determination of Parkinson’s sub types (Tremor; Akinetic Rigid; Mixed) relative to those derived from MDS-UPDRS ratings.
7. We will use established actigraphy methods (i.e. Geneactive) to measure the environmental light exposure and activity as previously used in our studies. Participants are asked to wear this watch-like device over the period of the study (6 weeks).

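### The only defined tremor outcome is dominant frequency, which a change in tremor amplitude alone does not move, so by itself it cannot show whether light changes the size of tremor

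*Combined protocol and SAP*

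**What the plan says.** Two places define the tremor outcome, and they agree. The supplement's endpoint list, under Other Secondary (motor), gives the change from baseline to weeks 4 and 6 in mean "dominant frequency both hands for resting and postural tremor". The Tremor part of the Supplementary Methods closes with the same outcome: "Dominant frequency both hands for resting and postural tremor".

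The Tremor text describes finger-mounted inertial sensors sampled at 1125 Hz and two tasks with four 30 s trials each. Processing consists of a 5-sample median filter, selection of the main axis by principal components, removal of the first and last 2.5 s, a 4th-order Butterworth filter from 0.5 to 40 Hz, and "the power spectral density calculated by the Welch method". What is kept from the spectrum is the position of its peak: "The location of dominant frequency for each trial was confirmed visually".

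The protocol is broader. Section 5.5, item 6, states: "Tremor will be quantified from the accelerometer signals in the time and frequency domain using our previously established methods". The primary aim in section 2.1 concerns "circadian/sleep behaviour and motor (i.e. gait, balance, tremor) function in optimally medicated people with PD", and section 3 expects "improved sleep and motor function". Section 2.2 lists tremor among the other secondary outcomes without naming a measure.

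**The concern.** A peak position says at which frequency the power is concentrated. It does not say how much power there is. The aims ask whether motor function, including tremor, improves, and a natural reading of improvement is that tremor becomes smaller. None of the listed outcomes measures that directly. The time-domain quantification planned in the protocol could have done so, but no such measure reached the outcome lists.

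What is at stake is interpretation. A null group-by-time result for dominant frequency could be read as light having no effect on tremor, when the size of tremor was never analysed. A difference in dominant frequency could be read as benefit or harm, although the plan gives no rule for reading it either way.

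**Working it through.** There is no stated figure to reproduce: the plan gives no effect size or standard deviation for tremor. The question is what the outcome responds to.

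**Algebra.** Let x(t) be the recorded acceleration and PSD(f) its power spectral density. If x(t) becomes a·x(t), then PSD(f) becomes a²·PSD(f). Multiplying a curve by a positive constant does not move its maximum, so the dominant frequency is the same for every a > 0. Halving the amplitude (a = 0.5) divides power by 1/0.5² = 4 and leaves the outcome unchanged.

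**Simulation of the stated processing.** From the Tremor section: 1125 Hz, 30 s trial, 5-sample median filter, 2.5 s cut from each end (25 s left), 4th-order Butterworth 0.5-40 Hz, removal beyond 6 SD, Welch spectrum. Assumptions not in the documents:

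- a 5 Hz oscillation with slight phase jitter;
- a fixed background made of a 9 Hz component of amplitude 0.05 plus white noise of SD 0.05;
- Welch segments of 4 s (0.25 Hz bins);
- one axis, so no principal-components step;
- values beyond 6 SD set to zero rather than interpolated;
- one simulated recording per setting.

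Two cases were run: the whole recording rescaled, and the oscillation rescaled over the unchanged background. RMS is the root of the integrated spectrum after band-pass filtering.

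| Amplitude a | Rescaled: peak (Hz) | Rescaled: RMS | Over background: peak (Hz) | Over background: RMS |
|---|---|---|---|---|
| 2 | 5.0 | 1.415 | 5.0 | 1.414 |
| 1 | 5.0 | 0.707 | 5.0 | 0.707 |
| 0.5 | 5.0 | 0.354 | 5.0 | 0.355 |
| 0.25 | 5.0 | 0.177 | 5.0 | 0.180 |
| 0.1 | 5.0 | 0.071 | 5.0 | 0.079 |
| 0.06 | 5.0 | 0.042 | 5.0 | 0.056 |
| 0.05 | 5.0 | 0.035 | 9.0 | 0.051 |
| 0.04 | 5.0 | 0.028 | 9.0 | 0.046 |
| 0.02 | 5.0 | 0.014 | 9.0 | 0.039 |
| 0 | – | – | 9.0 | 0.037 |

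Under pure rescaling the peak does not move over a range of 2/0.02 = 100-fold. Over the background it stays at 5.0 Hz down to a = 0.06, a reduction of 1 − 0.06 = 94%. At a = 0.05 and below it sits at 9.0 Hz, the frequency of the assumed background. The step point and the landing frequency follow from the assumed background, so they illustrate the behaviour and do not estimate it for this trial.

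RMS falls at every step in both cases. Over the background it levels off towards the background's own 0.037, so it is graded until the oscillation is close to background.

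**Other listed outcomes.** The MDS-UPDRS motor score is exploratory and is the Part III sum. The MDS-UPDRS tremor subscore appears only in protocol section 5.1, to classify motor phenotype. No tremor subscore is an outcome.

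**The case against.** The simulation holds the oscillation at 5 Hz and changes only its amplitude, so an unchanged peak is built in. Whether light shifts tremor frequency, or whether frequency and amplitude move together in patients, is physiology that the documents do not supply. This stands, and it limits the claim to a change in amplitude alone. Dominant frequency may also serve the subtype classification mentioned in protocol section 5.5, and the repeated MDS-UPDRS motor score gives partial cover. Both are fair. Neither supplies a listed measure of tremor size.

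Three stronger readings are tempting and are not supported.

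- *Complete suppression of tremor would be missed.* When the oscillation vanishes, the peak can move to whatever dominates the background, as the table shows. The shift is not graded and the plan gives no rule for reading it, but it is not invisible.
- *Recordings without tremor add pure noise to the group means.* Where the peak lands depends on the background, which the documents do not describe. Assumed white noise put the mean peak at roughly 8 to 14 Hz, and assumed 1/f noise put it at about 1 Hz with little spread. Each trial's peak was also confirmed visually. No criterion for a missing peak is given, but nothing shows that trials without a peak entered unchecked.
- *The missing direction of benefit is a defect peculiar to tremor.* The supplement also states none for polysomnography, DLMO, gait or balance.

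Finally, the documents supplied contain no statement that light had no effect on tremor. The risk concerns how a result would be read.

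**Conclusion.** The concern holds in this form: the only defined tremor outcome does not respond to a change in tremor amplitude alone, is not a graded measure of severity, and can step to a background-dependent value when tremor nearly disappears. By itself it cannot support a conclusion that light does or does not change the size of tremor, which the aims call for and which the protocol's time-domain quantification could have covered.

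The invariance is exact and rests on no assumption beyond rescaling. The 94% figure rests on the assumed background. Dominant frequency remains usable as a description of tremor. Tremor is one of several other secondary motor measures, so the primary sleep and DLMO outcomes are untouched. The power of an amplitude outcome cannot be computed, because the documents give no tremor effect size or SD.

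**What to change.** Add one amplitude outcome from the existing recordings: log power in a band around the dominant peak, or log RMS acceleration over 0.5-40 Hz. Derive it for each hand and task (2 × 2 = 4 series), with lower meaning better. Analyse it with the same mixed model as the other outcomes. On the log scale, halving the amplitude is a shift of ln 2 = 0.69 in RMS or ln 4 = 1.39 in power.

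Keep dominant frequency as the declared outcome rather than replacing it. Interpret it descriptively and only for recordings with a clear peak, under a written criterion for what counts as one. Draw no conclusion on tremor severity from it.

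Label the added analysis post hoc if it is introduced after unblinding. The supplement's methods are in the past tense, and Figure S2 and Table S1 already report results by named group, so that label probably applies.

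The cost is small: no new data, one more summary from spectra already computed, and one more secondary analysis, which carries less weight if results are already known.
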